### Outcomes

5.7

We will measure several outcomes of interest using the mentioned questionnaires.

#### Primary outcomes

5.7.1

Employment status: Participants will be asked to self-report their current employment status as full-time, part-time, or unemployed.Monthly income: Participants will be asked to report their monthly income in US dollars (Ecuador's national currency).Socioeconomic status: This variable will be assessed using the Survey of Socioeconomic Level Stratification Questionnaire, a validated tool used in Ecuador to measure the socioeconomic status of households (44). Participants will be asked a series of questions related to their household assets, income, and education level.

Objective verification (when consented): At endline and 12-month follow-up we will seek employer confirmation (short phone/email check), accept documentary evidence (e.g., contract or pay-stub upload), and record LinkedIn employment updates. Objective indicators will be used to triangulate self-reports.

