### Eligibility criteria and selection process for new dimensions

5.2

Low-income, women-at-risk university students and graduates will be invited through social media, university talks, and other channels to apply for the program. After conducting market research, we found that in the two main Ecuadorian cities, Quito and Guayaquil, the demand for data-intensive roles is greater. As a result, the program will be primarily promoted for women living in either of these two cities.

Participants in the program will be selected after a holistic application process, which will consist of three stages. During the first stage, the candidates have to submit an application form. They will be asked basic personal, academic, and socioeconomic information, as well as two short essay questions in which the applicant have to provide a brief description of their current personal situation and their motivation to apply, respectively. A grader will assign a maximum score of 3 for the “personal situation” short-essay question and a maximum score of 5 for the “motivation” one.

Applications with a “motivation” score of less than or equal to 1 which is considered low will be automatically rejected. Then, all applications with a “motivation” and “personal situation” combined score of less than or equal to 2 (25% out of 8 maximum points) will be rejected as well. All non-rejected applicants at this stage will advance in the application process. The reason behind the decision to reject applicants with low scores is to ensure that only the most motivated candidates are given the opportunity to advance to the next stage.

At the second stage, candidates will be invited to take a computer-based basic mathematical skills exam. Applicants who attend the mathematical skills test will also be invited to the final stage of the process, a 15 min interview. A group of four interviewers will ask applicants six broad questions regarding their socioeconomic status, time management skills, knowledge and interest in data, and the *New Dimensions* program. A rubric will be culturally designed to evaluate all applicants on the clarity of their answers, as well as their motivation.

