### Interventions and control groups

5.3

**Full intervention group:** Participants in this group will undergo comprehensive training encompassing both technical and soft skills. The technical curriculum covers a range of software programs including Microsoft Excel, Power BI, SQL, GitHub, R, Tableau, statistics, and Python. These technical sessions will be delivered remotely in one-hour seminars, four days a week, with each software program's training lasting between 2 and 5 weeks starting September 2025. In addition to technical training, participants will also engage in soft skills development through workshops focused on empowerment, employability, and public speaking. These workshops will consist of four-hour in-person sessions held on weekends, approximately every three weeks. To culminate their learning experience, participants will be required to complete and present a capstone project.

**Training dose and supports:** Technical modules total approximately 80–120 contact hours across Excel, Power BI, SQL, GitHub, R, Tableau, statistics, and Python (1 h sessions, 4 days/week, 2–5 weeks per module), complemented by weekly office hours and pre-class micro-tasks (15–30 min). Soft-skills workshops (empowerment, employability, public speaking) total ∼24 h (in-person, weekend sessions). The capstone requires ∼30–40 h of independent/team work culminating in a public presentation with rubric-based assessment.

**Partial intervention group:** This group will receive a more focused intervention, limited to workshops on empowerment, employability, and public speaking. This targeted approach allows for the assessment of the specific impact of soft skills training on participant outcomes.

**Control group**: Comprising individuals who just miss the cut for full program admission, this group will not receive any intervention. This setup enables a clear comparison to be made between those who receive interventions and those who do not, providing insight into the program's overall effectiveness. Participants for both the partial intervention and control groups will be selected randomly from a pool of applicants who narrowly miss selection for the full intervention, ensuring no significant differences in observable characteristics among the groups.

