### Sample size

5.8

The sample size for this study will consist of 80 participants, including 50 in the full intervention group, 20 in the soft skills-only group, and 10 in the control group. This study is exploratory in nature due to resource constraints, particularly funding limitations and logistical challenges in delivering training sessions. The sample size was determined based on the maximum feasible recruitment capacity within the available resources rather than a formal statistical power calculation. While a larger sample would enhance the statistical power of the findings, this study serves as an initial investigation into the effectiveness of the New Dimensions program, providing preliminary evidence that can inform future large-scale studies and programs.

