### Assignment of interventions

5.10

The full intervention group, comprising both hard and soft skills training, will be selected from the full pool of applicants based on economic need, academic, and motivational merit by a team of four reviewers. Thus, owing to the nature of this application process, the intervention for the full group will not be randomly assigned. A pool of applicants who narrowly misses being selected for the full intervention group will be created. Participants from the soft skills-only (partial intervention) and control groups will be randomly selected using Microsoft Excel's random-number generator function. Random selection will be conducted within strata defined by city (Quito/Guayaquil), baseline employment status (employed vs. not), and motivation score tertiles to minimize imbalance. Excel RAND() will be used to generate random numbers separately within each stratum, followed by rank-ordering and assignment.

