### Statistical plan

6.3

Descriptive statistics will be used to summarize the demographic characteristics of the study population and examine the distribution of outcome variables. Continuous variables will be summarized as means and standard deviations or medians and interquartile ranges depending on their distribution. Categorical variables will be summarized as frequencies and percentages.

To assess the effectiveness of the *New Dimensions program*, we employ a quasi-experimental design with two intervention groups and one control group. The two intervention groups will be compared to the control group to evaluate the impact of the program on employability and well-being outcomes.

To test for differences in baseline characteristics between the intervention and control groups, we used *t*-tests for continuous variables and chi-square tests for categorical variables. To examine changes in the outcome variables over time, we plan to employ linear mixed-effects regression models. Models will include fixed effects for group (full/partial/control), time (baseline/endline/12-month), and the group × time interaction (primary estimand), with random intercepts for participants. These models will allow us to account for the within-subject correlation of repeated measurements over time and adjust for potential confounders, such as age and educational level. We will additionally adjust for city, baseline employment status, and motivation score (tertiles). This will help to control for variations in motivation that could impact outcomes, thereby reducing the risk of false positives. By adjusting for motivation, we aim to ensure that the observed effects are more likely to be attributable to the intervention itself rather than pre-existing differences between groups.

Missing data will be handled using complete case analysis when the proportion of missing data is low and assumed to be missing completely at random (MCAR). For cases where missingness is more substantial, we will implement inverse probability weighting (IPW) to adjust for potential differences between participants who remain in the study and those lost to follow-up. Descriptive comparisons between retained and lost participants will also be performed to assess systematic differences that could influence the results.

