All statistical tests will be two-sided, with a significance threshold of *p* < 0.05. Missing data will be addressed using Multiple Imputation by Chained Equations (MICE) under MAR assumptions, with sensitivity analyses including complete-case and IPW approaches. Given the exploratory sample size (*n* = 80), we will emphasize precision of estimates (95% confidence intervals) rather than sole reliance on *p*-values, and will apply small-sample robust standard errors where appropriate. All analyses will be conducted in Stata 19.0.

To prevent undisclosed flexibility in our analysis pipeline, as mentioned before, we have predefined all primary and secondary outcomes and will adhere strictly to the outlined statistical methods. Outcome-neutral conditions are established by employing validated instruments known to avoid floor or ceiling effects. Given that the study is exploratory due to funding and resource constraints, no formal power calculation was performed. Therefore, some analyses, particularly those involving subgroup comparisons (e.g., differences between full and partial intervention groups), should be considered exploratory. Assumptions for our analyses include approximate normality of continuous variables and that data are missing at random (MAR), both of which will be examined through diagnostic and sensitivity checks. Missing data will be addressed using Multiple Imputation by Chained Equations (MICE) under MAR assumptions, and effect sizes with 95% confidence intervals will be reported and compared across imputed and complete-case approaches. Robustness will be evaluated by repeating models both with and without adjustment for baseline motivation scores. Finally, to address potential selection bias from the non-random assignment of participants to the full-intervention group, we will perform propensity-score inverse probability of treatment weighting (IPTW) sensitivity analyses based on age, education, city, baseline employment status, and motivation score.

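### The employment item codes a student not seeking work like a job-seeking graduate, and no stratum, covariate or weight names enrolment, so unequal student shares could bias the full-versus-control comparison

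*Protocol article*

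**What the plan says.** - Population (Eligibility criteria and selection process): "Low-income, women-at-risk university students and graduates will be invited through social media, university talks, and other channels to apply for the program".
- Employment outcome (Primary outcomes): "Participants will be asked to self-report their current employment status as full-time, part-time, or unemployed". No state for studying or for being outside the labour force is named.
- Timing (Baseline, endline, and follow-up assessments): baseline in the month the program starts, endline at completion, follow-up one year after that. Training pace (Interventions and control groups): "1 h sessions, 4 days/week, 2–5 weeks per module", for eight technical subjects, with 80–120 contact hours in total.
- Group sizes (Sample size): "80 participants, including 50 in the full intervention group, 20 in the soft skills-only group, and 10 in the control group".
- Allocation (Assignment of interventions): four reviewers choose the full group on need, academic record and motivation. The other two groups are drawn at random from the near-miss pool: "Random selection will be conducted within strata defined by city (Quito/Guayaquil), baseline employment status (employed vs. not), and motivation score tertiles".
- Analysis (Statistical plan): a linear mixed model with group, time and their interaction, the interaction being the primary estimand. The model is to "adjust for potential confounders, such as age and educational level", and also for city, employment at baseline and motivation tertile. Inverse probability of treatment weighting on age, education, city, baseline employment and motivation is a sensitivity analysis.

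**The concern.** Two related problems arise, and they are best kept apart.

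The first is the response set. The three states have no truthful place for a full-time student who is not seeking work except the one used for a job-seeking graduate. The stratum of employed versus not pools the same two kinds of women.

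The second is confounding of the time course. Students who finish their degrees during the study can be expected to move into work in larger numbers than women who had already graduated. If one group holds more students near graduation than its comparator, a group × time difference in employment appears with no program effect, and income could be affected in the same way. None of the named design or analysis variables is enrolment status. The full group is selected on criteria, including academic background and the ability to balance other commitments, that may well be related to enrolment.

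At stake is whether a difference in employment reflects the training or the mix of students and graduates.

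**Working it through.** **Group sizes.** 50 + 20 + 10 = 80, which matches the stated total. The protocol states no power figure, effect size or variance; the number is the "maximum feasible recruitment capacity within the available resources rather than a formal statistical power calculation".

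**Observation window** (4.348 weeks per month).
- From module lengths: 8 × 2 = 16 weeks to 8 × 5 = 40 weeks, or 3.7 to 9.2 months. Adding 12 months gives 15.7 to 21.2 months.
- From contact hours: 80/4 = 20 weeks to 120/4 = 30 weeks, or 4.6 to 6.9 months. Adding 12 gives 16.6 to 18.9 months.

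Both routes leave time for some students to graduate.

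**Bias in group × time.** With no program effect,

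bias = (student share in intervention group − student share in control) × (employment gain in students − employment gain in graduates).

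The protocol gives neither factor, so the values below are assumptions.

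| Share gap | Gain difference 20 points | 30 points | 40 points | 50 points |
|---|---|---|---|---|
| 0 | 0 | 0 | 0 | 0 |
| 10 points | 2 | 3 | 4 | 5 |
| 20 points | 4 | 6 | 8 | 10 |
| 30 points | 6 | 9 | 12 | 15 |
| 40 points | 8 | 12 | 16 | 20 |

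The sign follows the direction of the share gap.

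**Does a main effect remove it?** A simulation of 50 full versus 10 control used two time points and no program effect. Employment rose from 30% to 70% in students and stayed at 50% in graduates. Estimated group × time:

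| Student shares, full vs control | No student term | Student main effect | Student × time |
|---|---|---|---|
| 50% vs 50% | 0.007 | 0.007 | 0.007 |
| 60% vs 30% | +0.121 | +0.121 | 0.000 |
| 30% vs 60% | −0.121 | −0.121 | −0.003 |

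The formula gives 0.30 × 0.40 = 0.12, in agreement. The 0.007 is simulation error. Even a main effect for student status itself leaves the bias untouched, so one for educational level cannot do better. Only the interaction with time removes it.

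**Chance imbalance.** If the two groups were random draws with a 50% student share, the SD of the share difference would be √[0.25 × (1/50 + 1/10)] = 0.173 for full versus control and √[0.25 × (1/20 + 1/10)] = 0.194 for partial versus control. For the second comparison, which the protocol says is randomly drawn, this is sampling variation. For the first, a random-draw calculation cannot describe a group selected on merit.

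**The case against.** **Graduation is not in itself credited to the program.** A reader might infer that it is. The estimand is an interaction against a concurrent control group, so graduation common to the groups cancels. The equal-share row above shows this. This part of the objection stands in full.

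**Chance imbalance is not bias.** With 10 controls, any unstratified prognostic factor will be unbalanced in many replications. An exact binomial calculation gives a student-share gap of 20 points or more with probability about 0.28 for 50 versus 10 and 0.37 for 20 versus 10, assuming 50% students. It would be wrong to read these as probabilities of a biased trial. For partial versus control they describe imprecision that belongs in the confidence interval. This also stands.

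**A continuing student is not scored as a failure.** One might read the three categories that way, but the protocol defines no success or failure on employment. Under employed versus not, a student without a job is not employed whether or not a fourth state exists. The new response clarifies what was measured; it does not by itself cure the confounding.

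**The effect is small beside the noise.** If the within-person change in employment has variance 0.25 to 0.4 (an assumption), the standard error for full versus control is √[0.25 × 0.12] = 0.17 to √[0.4 × 0.12] = 0.22. Six points is about a third of that, in a study labelled exploratory. This limits the weight of the point. Yet imprecision shows in the interval, and a shift from unequal student shares does not.

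**Education may already capture enrolment.** The demographic questionnaire covers education and the application form covers academic information, so enrolment may be recorded; the article does not say. If education is coded to separate degrees in progress from completed ones, weighting on it could balance student shares. That coding is not stated, and the weighting is only a sensitivity analysis. The objection stands in part.

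**Conclusion.** The point holds in a limited form. The stated response set merges two different labour-market states in a primary outcome. Enrolment status is absent from the strata, the named covariates and the named weighting variables. Full versus control is open to bias if student shares differ, because selection into the full group is not random and rests partly on academic merit. The protocol shows neither that the shares will differ nor in which direction. Partial versus control is affected through imprecision only.

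The size cannot be fixed from the protocol. Over share gaps of 10 to 40 points and gain differences of 20 to 50 points, all assumed, the bias runs from 2 to 20 points in either direction; it is zero when shares are equal. This is a worthwhile and cheap improvement, not a flaw that invalidates the design.

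**What to change.** 1. Add a fourth employment response: not in the labour force (studying or caring, not seeking work).
2. Record enrolment status and expected graduation date at baseline, and current enrolment at each later visit. If the application form or demographic questionnaire already holds the baseline items, say so and use them.
3. Prespecify the employment outcome as employed versus not, with baseline enrolment status and its interaction with time in the model. Given 10 controls, a prespecified sensitivity analysis is the minimum.
4. Add enrolment status to the variables in the treatment-weighting analysis.
5. Report the student share by group at baseline, so that readers can judge whether the problem arose.

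The cost is one response option, a few short items, one further model interaction and one more weighting variable. The downside is a slight loss of precision in comparisons with the control group.

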### Questionnaires

5.4

The following validated questionnaires, widely used in Spanish-speaking populations, will be administered to gather comprehensive data from the participants, assessing various aspects of their demographic background, health, socioeconomic status, food security, and quality of life:
General Demographic Questionnaire: This questionnaire will gather basic information about the participants, such as age, education, and employment status.SF-36: This is a widely used self-reported measure of health status that assesses eight domains of health-related quality of life: physical functioning, role limitations due to physical health, bodily pain, general health perceptions, vitality, social functioning, role limitations due to emotional problems, and mental health (43).Survey of Socioeconomic Level Stratification: A questionnaire will be employed to know about the socioeconomic status of the participants based on factors such as income, education, and occupation (44).HFIAS (The Household Food Insecurity Access Scale): This is tool used to assess household food insecurity (45). It will provide insight into the participants' access to nutritious and adequate food.Latin American-Spanish adaptation of the WHOQOL-100 (World Health Organization Quality of Life Questionnaire: This is a self-reported questionnaire that assesses an individual's subjective perception of their quality of life across four domains: physical, psychological, social, and environmental (46).Each of the validated questionnaires that will be used in this study is available in detail through their respective references provided in the manuscript. These references include comprehensive information on the structure, application, and validation of each tool.

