### Contingency plan

5.6

To mitigate any potential challenges that may arise during the implementation of the program, such as participant dropout, logistical delays, or incomplete data collection, we have developed a contingency plan. If participants drop out, we will recruit from a waitlist of eligible candidates to maintain group sizes. For logistical issues, such as delays in workshops or technical difficulties in remote training, we will offer alternative scheduling or supplemental online materials. Additionally, if data collection is incomplete, we will send reminders and offer flexibility in deadlines for questionnaire submissions. These measures ensure that the study can proceed as planned and still provide robust results.

Retention protocol: We will use a standardized contact cadence (SMS/Whastapp/email at T + 3, T + 7, T + 14 days from survey invitation; phone call at T + 21), modest incentives at endline/follow-up, and alternate contacts captured at baseline. Non-responders will be re-contacted in two additional waves at 2-week intervals.

To effectively minimize research biases, the study incorporates clearly defined eligibility criteria and randomized participant assignment for the partial intervention and control groups, significantly reducing selection bias. We will also conduct propensity-score IPTW sensitivity analyses to address potential baseline imbalances. Measurement bias is controlled by employing validated data-collection instruments and standardized interviewer training, ensuring consistency across assessments. Furthermore, attrition bias will be actively managed through systematic follow-ups, routine participant reminders, and timely replacement of dropouts using the established waitlist.

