### Data collection methods

6.1

Candidates will submit an online application form in which they have to provide demographic and socioeconomic information as well as their motivation to apply to the program. After submitting this form, the shortlisted candidates will be asked to take a computer-based exam to collect information on their math skills. Applicants will be encouraged to answer all questions. Each candidate who advances to the next stage of the selection process will be interviewed by members of the program's admission committee. All interviewers will record and score their responses. At follow-ups, we will implement the objective employment verification procedures (employer check, optional document upload, LinkedIn observation) for consenting participants.

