### Ethics

6.4

This research project was approved by the Institutional Review Board (IRB) of Kennedy Clinic in Guayaquil, with approval code HCK-CEISH-2022-006. Written informed consent will be obtained and will be required at every stage of the research in accordance with ethical guidelines for human subjects' research.

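### Employment status and income have no stated fallback source when a woman does not complete the survey, although the planned call and re-contact waves could supply one

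*Protocol article*

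**What the plan says.** - **Source of the outcomes.** Section 5.7 opens: "We will measure several outcomes of interest using the mentioned questionnaires". Section 5.7.1 then says of employment "Participants will be asked to self-report their current employment status as full-time, part-time, or unemployed" and of income "Participants will be asked to report their monthly income in US dollars". Section 5.4 places employment status in the General Demographic Questionnaire: "This questionnaire will gather basic information about the participants, such as age, education, and employment status". The other instruments are the SF-36, the socioeconomic stratification survey, the HFIAS (nine food-insecurity questions) and the WHOQOL-100 (100 items).
- **Verification.** Section 5.7.1 describes employer confirmation, documents and LinkedIn updates at endline and 12 months, subject to consent. Their stated use is: "Objective indicators will be used to triangulate self-reports". Section 6.1 repeats the procedures, ending "optional document upload, LinkedIn observation) for consenting participants".
- **Contact of non-responders.** Section 5.6 sends messages 3, 7 and 14 days after the survey invitation and makes a call at day 21. It adds: "Non-responders will be re-contacted in two additional waves at 2-week intervals". Incomplete data are met with reminders and flexible deadlines, and dropouts are replaced from a waitlist.
- **Analysis of what stays missing.** Section 6.3 names multiple imputation under missing at random, inverse probability weighting, and complete-case analysis when little is missing and it is assumed missing completely at random.

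**The concern.** Employment and income are the outcomes the program is meant to change, and they can be asked in two short questions. The plan already pays for a call, two further waves, alternate contacts and an employment check. None of these is given the stated task of obtaining the two answers from a woman who has not returned the survey. Verification is tied to a self-report, so where there is no self-report its result has no stated role.

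This matters if the reason for silence is the outcome itself, for example a new job that leaves less time. Every missing-data method in section 6.3 assumes that missingness can be explained by observed data or is completely random. None allows it to depend on a job that was never recorded. Unequal loss by arm is plausible: in section 5.2 the 50/20/10 split is justified partly by lower anticipated engagement in the partial group and possibly lower motivation among controls. With ten controls, each woman is 10 points of her arm.

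**Working it through.** **Inputs from the protocol.** Arms of 50, 20 and 10 (section 5.8); 50 + 20 + 10 = 80, which reproduces the stated total. There is no power calculation, attrition rate or expected employment share, so every rate below is an assumption.

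**1. Bias from arm-specific loss (complete cases).** In one arm, observed share − true share = −(fraction lost) × (employment share of lost women − share of retained women). Assume a gap of 20 to 40 points in both arms, with lost women more often employed.

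- Full arm, 10% lost (5 of 50): 0.10 × 20 to 40 = 2 to 4 points too low.
- Control, 30% lost (3 of 10): 0.30 × 20 to 40 = 6 to 12 points too low.
- Full minus control: 6 − 2 = 4 to 12 − 4 = 8 points too high.

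**2. The same question through response rates.** With true employed share *p*, and response rates *rE* among employed and *rU* among not-employed women:

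observed share = *p·rE* / (*p·rE* + (1 − *p*)·*rU*).

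Assume true shares of 0.60 (full) and 0.40 (control), so a true difference of 0.20, with *rU* = 0.90. Where an arm has no job-related loss, *rE* = 0.90 too.

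| *rE* where loss is job-related | Full arm only | Control only | Both arms equally |
|---|---|---|---|
| 0.80 | 0.171 | 0.228 | 0.199 |
| 0.70 | 0.138 | 0.259 | 0.197 |
| 0.60 | 0.100 | 0.292 | 0.192 |

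Example, full arm only, *rE* = 0.60: 0.36 / (0.36 + 0.36) = 0.50, and 0.50 − 0.40 = 0.10. Control only: 0.24 / (0.24 + 0.54) = 0.308, and 0.60 − 0.308 = 0.292.

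The contrast is sensitive to loss that differs between arms, in either direction. It is almost insensitive to equal loss.

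**3. What the missing answers leave undetermined.** The worst-case range for full minus control has width (missing in full)/50 + (missing in control)/10.

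- 5 and 1 missing: 0.10 + 0.10 = 20 points.
- 10 and 2 missing: 0.20 + 0.20 = 40 points.
- 10 and 3 missing: 0.20 + 0.30 = 50 points.

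Each control whose status is obtained removes 10 points of this width, and each full-arm woman removes 2.

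**4. Scale against sampling error.** With 50 against 10 and half of each arm employed, the 95% half-width is 1.96 × √(0.25/50 + 0.25/10) = 0.339, or about 34 points.

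**The case against.** The strongest reply is that much of this is read from silence. The article does not say what is asked on the call or in what order the items come, and a condensed article may leave both to the full protocol. Retention is also treated seriously: four timed contacts, two more waves, incentives, alternate contacts, and a comparison of retained with lost women. A bias of 4 to 8 points is small beside an interval of about ±34 points in a study declared exploratory. The arithmetic is for complete cases, whereas imputation is planned and may recover the part of the loss that baseline data predict.

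These replies limit the size of the point. What stands is that the article does state a use for verification, and that use is confined to checking self-reports. It also states a remedy for incomplete data, which is reminders and later deadlines. Bias of this kind is not shown by the confidence interval.

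Several stronger readings are tempting, and the document does not support them:

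- *That the two items are lost whenever a woman does not finish a long battery.* The SF-36 (36 items, from its name), WHOQOL-100 and HFIAS come to 36 + 100 + 9 = 145 items. But section 5.4 lists separate questionnaires with the demographic form first, and nothing makes completion all-or-nothing.
- *That a non-responder cannot be verified.* Section 6.4 says "Written informed consent will be obtained and will be required at every stage of the research", which does not bar checking someone who has already consented. Nor is verification tied to attending training.
- *That the call serves only to chase the survey.* It is timed from the survey invitation, but its content is not given.
- *That getting a job will cause non-response.* This is a reasonable assumption, but no section states it.
- *That the error could reach 8 to 16 points.* With the loss rates in step 1, that needs gaps of opposite sign in the two arms. Non-response caused by finding a job gives the same sign in both.

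**Conclusion.** The point holds as a cheap improvement to data collection. As written, employment status and income rest on questionnaire self-report, verification only supports those self-reports, and the planned contacts have no stated fallback for the two items. If non-response depends on having found a job and differs by arm, the planned analyses would not remove the resulting bias. Under the assumed 10% and 30% losses and a same-sign gap of 20 to 40 points, the complete-case contrast is off by about 4 to 8 points. Under equal job-related loss, the 0.20 difference used in the illustration falls only to between 0.199 and 0.192. The direction depends on which arm loses more employed women, which the collected data would not reveal. Socioeconomic status, the third primary outcome, needs its own questionnaire and is not helped by this change.

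**What to change.** **Section 5.6.** Place employment status and monthly income first in each survey. State that the day-21 call and the two re-contact waves are used to take these two items orally from every enrolled woman who has not completed the survey, including women who stopped training or were replaced from the waitlist. Record the mode of collection.

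**Sections 5.7.1 and 6.1.** State that verification is also attempted for non-responders who have already consented to it, and that the result is supporting evidence on employment status in a sensitivity analysis. Absence of a LinkedIn entry must not be read as unemployment. Expect limited yield: the employer in a new job may be unknown, and neither employer confirmation nor LinkedIn is said to give income.

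The stage-wise consent in section 6.4 stays as it is.

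**Cost.** Protocol wording, item order and a two-question call script, using contacts already planned. The downside is mixed mode: some answers come by telephone and others online, which is why the mode should be recorded. The change should be in place before endline, because an answer about status at that time is hard to obtain later.
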